# Strengthening Primary Care for Recognising and Treating Depression (SPiRiT-D): a study protocol for a cluster randomised controlled effectiveness-implementation trial of collaborative care for depression

**DOI:** 10.1186/s13063-026-09453-5

**Published:** 2026-01-28

**Keywords:** Collaborative care, Depression, Hybrid Type II, Implementation strategies

## Abstract

**Background:**

The effectiveness of collaborative care for treating depression in primary care has been well-established in high-income countries and, more recently, in a few trials in low- and middle-income countries (LMICs). However, evidence for its effectiveness, costs and how it can be implemented in ‘real-world’ settings within resource-constrained health systems in LMICs is currently limited. We aim to investigate the implementation, clinical and cost-effectiveness of a contextually adapted collaborative care model for depression in primary care clinics in Pakistan.

**Methods:**

A hybrid type-II effectiveness-implementation cluster randomised controlled trial with embedded process and economic evaluations will be conducted. Twenty-four primary care clinics located in socioeconomically disadvantaged areas of Karachi will be randomly allocated (1:1) using minimisation to either (i) a contextually adapted collaborative care model for depression supported by co-designed implementation strategies or (ii) optimised usual care (routine practice with additional depression screening and provision of information leaflets about depression for those screening positive). Participants aged 18 years or above, scoring ≥ 10 on the 9-item Patient Health Questionnaire (PHQ-9) and not under any active treatment for depression, will be recruited. The Reach, Effectiveness, Adoption, Implementation and Maintenance framework will guide our outcome evaluation. The primary clinical outcome will be depression severity, assessed using the PHQ-9 at 6 months after participant recruitment. The primary implementation outcome will be ‘reach’ (proportion calculated as the number of people who participated in depression treatment divided by those eligible for such treatment) using routine, clinic-level aggregated data at 6 months. The process evaluation will explore factors such as fidelity, acceptability and sustainability of collaborative care using a mixed-methods approach guided by the Consolidated Framework for Implementation Research. A within-trial economic evaluation will explore the cost-effectiveness of both collaborative care and implementation activities. Individual-level effectiveness outcomes will be analysed using mixed-effect linear regression; and clinic-level implementation outcomes using generalised linear regression. Trial data analysis will be based on an intention to treat principle.

**Discussion:**

If collaborative care is shown to be successfully implemented, clinically, and cost-effective, it will provide health and economic benefits for people with depression presenting in primary care. It will also be a means to strengthen primary care services through a trained workforce that can recognise and manage depression, improve information management systems, and promote evidence-based care.

**Trial registration:**

ISRCTN13462277 prospectively registered on 07 October 2024 10.1186/ISRCTN13462277.

**Supplementary Information:**

The online version contains supplementary material available at 10.1186/s13063-026-09453-5.

## Background

Depression is one of the most common of all mental disorders, affecting 280 million people globally, with a higher number of cases in women (170 million) compared to men (109 million) [1]. It significantly impacts the lives of those who are affected, their families and society [2]. The negative effects are far reaching, hindering access to educational, occupational, and economic opportunities [3]. The presence of depression in individuals with physical illness worsens outcomes for both conditions, resulting in earlier and higher mortality rates, as well as increases in healthcare costs [4, 5].

Treatment coverage for depression is poor in many parts of the world and this is particularly true for low- and middle-income countries (LMICs). Only 8% of individuals identified with depression receive mental health services in LMICs, compared to 33% in high-income countries (HICs) [6]. Many countries still lack the healthcare infrastructure, mental health policy, legislation, or adequate resources to deliver mental health programmes [7]. Pakistan is an LMIC and is the fifth most populated country in the world. Epidemiological evidence suggests a high rate of depression, 6% in the general population [8] surpassing the 5% global prevalence rate [9]; which may still be an underrepresentation of the actual prevalence. Despite underreporting, depression is now the second major cause of disability in Pakistan [4]. Tackling depression is, therefore, a high priority, especially in the wake of COVID-19, recent political and economic crises and natural disasters such as floods, resulting in the loss of lives, homes and economic opportunities, increasing the population’s vulnerability to mental disorders. Compounding the challenge, the current healthcare infrastructure, workforce and financing are significantly under-resourced to address the rising burden of mental disorders [10].

Training non-specialists in primary care to deliver evidence-based treatments for depression could be a possible solution. The World Health Organization (WHO) advocates for integrating low-cost mental health services in primary care and offers a range of guidance, training and supporting material to implement this in practice [11]. Among the various mental health care delivery models, the collaborative care (CC) model stands out as the most extensively tested and supported by robust evidence [12, 13]. CC is a low-cost, joined-up, integrated and patient-centred model of service delivery for physical and mental health, appropriate for primary care settings [14]. One of the notable aspects of the CC model is task sharing, in which non-specialists are trained to provide mental health care under supervision of mental health specialists. Other key components of CC include (i) population-level identification of depression; (ii) provision and adjustment of evidence-based care; (iii) tracking treatment outcomes and (iv) case review meetings [14, 15].

Evidence-based treatment for depression includes the delivery of psychotherapy and/or antidepressants [16, 17]. There is considerable evidence that non-specialist healthcare workers can be trained to deliver brief but effective psychological treatments for common mental disorders [18, 19]. Mild to moderate cases can be managed by non-specialists, while severe or treatment-resistant cases are referred to mental health specialists, this is known as the ‘stepped-care’ approach.

Behavioural activation (BA) is a relatively simple and flexible psychological therapy which has been proven to be effective for the treatment of depression [20], and can be delivered using a CC model. It is recognised for its parsimony, portability across cultures and efficiency of training [21–23]. It works by identifying activities that the person with depression may be avoiding due to loss of motivation or feeling overwhelmed as a consequence of being depressed. The focus of BA is to break the cycle of depression and to re-engage people with stable and diverse sources of positive reinforcement from the outside world and to develop depression management strategies for future use [22].

The clinical and cost-effectiveness of the CC model has been tested in many HICs [24] with evidence indicating CC leads to significant improvements in depression and anxiety, while also reducing associated healthcare costs [25–27]. A recent systematic review also reported effectiveness of CC in LMICs for improving depression outcomes at short (3 months), medium (6 months), and long-term (12 months) follow-ups [13]. However, this evidence is limited, particularly for South Asian countries, with only three trials conducted [28–30].

Despite the known clinical effectiveness of CC, there is a considerable evidence-implementation gap [31, 32], which is more pronounced in resource-limited settings in LMICs, where the implementation of evidence-based practices is not well-understood [33]. Evaluating the implementation and effectiveness of CC in diverse contexts, particularly in LMICs, could offer valuable insights. We therefore aim to evaluate the implementation, clinical effectiveness and cost-effectiveness of CC, using co-designed implementation strategies, for improving depression outcomes in primary care clinics in Pakistan.

## Objectives

Our specific objectives are to:Evaluate the implementation, clinical effectiveness, and cost-effectiveness of the CC model for depression compared to optimised usual care.Assess the fidelity, quality and acceptability of the CC model and identify the mechanisms of change and contextual factors associated with implementation outcomes.

## Methods

### Study design

The study design is an effectiveness-implementation hybrid type-II trial with cluster randomisation to evaluate CC in primary care clinics in Karachi, Pakistan. A mix of qualitative and quantitative methods will be used to collect data on clinical effectiveness, and implementation outcomes. An embedded process evaluation will help to understand implementation processes, and an economic evaluation will assess cost-effectiveness. Trial registration data is presented in Table 1. The SPIRIT reporting checklist is included as additional information [34].

**Table 1 Tab1:** Trial registration data

Data category	Information
Primary registry and trial identifying number	ISRCTN ISRCTN13462277
Date of registration in primary registry	October 07, 2024
Source(s) of monetary or material support	NIHR under Global Health Research Centre programme (NIHR203248)
Primary sponsor	The University of York, UK
Contact for public inquiries	[name]
Contact for scientific queries	[name]
Public title	Improving services for identifying and treating depression in primary healthcare clinics
Scientific title	Strengthening Primary care for Recognising and Treating Depression (SPiRiT-D)
Countries of recruitment	Pakistan
Health condition(s) or problem(s) studied	Depression
Intervention(s)	The intervention involves implementing a collaborative care model for depression in primary healthcare units. This model includes five key components: systematic identification of depression, provision and adjustment of evidence-based care (both antidepressants and brief behavioural treatment), tracking treatment outcomes, and weekly case review and supervision meetings. A collaborative care model for identifying and managing depression will be introduced in all intervention clinics using various implementation strategies
Key inclusion and exclusion criteria	Inclusion criteria: 1. Attending primary care clinics, 2. Aged 18 years or above, 3. Score on PHQ-9 ≥ 10 Exclusion criteria: 1. Participants already receiving any kind of treatment for depression, 2. Participants lacking the capacity to provide informed consent, or not willing to consent
Study type	Effectiveness-implementation hybrid type II cluster randomised controlled trial with an embedded economic and a mixed-methods process evaluation
Date of first enrolment	June 02, 2025
Target sample size	750
Recruitment status	Recruiting
Primary outcome(s)	1. Effectiveness: Depression severity (mean change) measured using Patient Health Questionnaire-9 (PHQ-9) at the 6-month timepoint 2. Implementation: Reach of depression treatment (RT) using RT = st/ne, where ‘st’ represents the number of individuals who participated in the treatment for depression and ‘ne’ represents the number of people eligible for such treatment at 6 months
Key secondary outcome(s)	The following secondary outcomes related to clinical effectiveness will be measured at the participant level during follow-ups at 3, 6, and 12 months, unless otherwise specified below: 1. Body mass index (BMI) calculated using the formula: BMI = weight (kg)/height (m^2^), where height is measured in metres and weight is measured in kilograms 2. Blood pressure measured using an automated blood pressure instrument 3. Waist circumference measured in centimetres 4. Depression severity measured using PHQ-9 at 3 and 12 months 5. Depression caseness measured using PHQ-9 6. Anxiety caseness and severity measured using Generalised Anxiety Disorder Questionnaire (GAD-7) 7. Quality of life measured using Euroqol’s instrument EQ-5D-5L 8. Functional impairment measured using the WHO Disability Assessment Schedule (WHODAS 2.0) at 6 and 12 months 9. Healthcare resource measured using modified Client Service Receipt Inventory (CSRI) at 6 and 12 months 10. Adverse events measured using a modified adverse event The following clinic-level aggregated secondary outcomes related to implementation effectiveness will be calculated at 3, 6, and 12 months follow-up timepoints, unless otherwise specified below: 11. Reach of screening (RS) calculated using the formula RS = sd/nc, where ‘sd’ represents the number of individuals screened for depression and ‘nc’ denotes the total number of individuals attending the clinics 12. Reach of depression treatment (RT) calculated using RT = st/ne, where ‘st’ represents the number of individuals who participated in the treatment for depression and ‘ne’ represents the number of people eligible for such treatment at 3 and 12 months 13. Adoption (AD) calculated using AD = r/nr, where ‘r’ denotes the number of people referred for the treatment of depression and ‘nr’ denotes the number of people eligible for referrals at 3, and 6 months 14. Treatment enrolment (TE) calculated using TE = te/ne, where ‘te’ represents the number of people enrolled in the treatment of depression and ‘ne’ represents the number of people eligible for such treatment 15. Treatment completion (TC) calculated using TC = tc/te, where ‘tc’ represents the number of people completed the depression treatment and ‘te’ the number of people enrolled in such treatment 16. Treatment drop (TD) calculated using TD = td/te, where ‘td’ represents the number of people dropped out of the depression treatment and ‘te’ the number of people enrolled in such treatment 17. Sustainability calculated using change in percentage from baseline to follow-up time-points in reach, adoption, treatment enrolment, completion, and dropout 18. Equity by comparing reach, adoption, treatment enrolment, completion, and dropout across different levels of socioeconomic status, gender, and ethnicity

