### Recruitment

Recruitment of patients will be based on a two-stage screening process. All patients attending the trial clinics will be screened by trained PCPs for depressive symptoms initially using the PHQ-2 (a brief version of PHQ-9). Patients screening positive on PHQ-2 (score ≥ 3) will be referred to the counsellors for assessment using the PHQ-9. This will be implemented as part of routine practice in both the intervention and control clinics. To balance the intervention and control clinics except for the intervention, we plan to recruit counsellors for those trial clinics which do not have counsellors present currently.

In the intervention clinics as part of the CC model, patients who screen positive on PHQ-9 (score 10 or above) will be offered BA therapy, antidepressants, or their combination as per treatment protocol. In control clinics, optimised usual care (OUC) will be offered, including information leaflets and routine psychological treatment. Patients who fulfil the trial inclusion criteria will be approached by the researcher present, who will provide the study information sheet in the local language. Written informed consent will be obtained before trial enrolment. Where there are issues of literacy, the information will be read out by researchers and understanding checked; consent will be recorded via thumbprint signatures. Potential participants will be informed that their decision to take part in the study will not affect their entitlement to usual services and that they are free to withdraw from the study at any stage without having to provide a reason. If participants are willing to provide reasons for withdrawal, this will be recorded in the change of status form. There are no cross-overs intended as part of the trial design, and cross-overs of the trial participants between the intervention and control clinics are less likely to happen because of the separate catchment areas that the different clinics serve. However, the central electronic records system will help identify any potential cross-overs, in the unlikely case of it happening.

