#### Collaborative care model

The CC components co-designed considering the SINA context include the following: (i) two-stepped systematic identification of depression for all people aged ≥ 18. In the first stage, PCPs will screen patients using the PHQ-2, those scoring ≥ 3 will be referred to the lay counsellor. In the second stage, the counsellors will use the PHQ-9 to identify depression; (ii) counsellors will offer BA [38] therapy to patients scoring ≥ 10 on the PHQ-9. If a patient does not respond or prefers antidepressants, counsellors will refer the patient to the PCP to initiate antidepressant treatment; (iii) counsellors will track and monitor depression (e.g. the severity of depression symptoms) and process measures (e.g. number of contacts, care provided, and review with the mental health specialist) for all patients currently receiving care; (iv) counsellors and PCPs will collaboratively adjust care, using a stepped care approach such as augmenting BA with medication or changing the medication dose until care goals (improvement or remission of depression) are achieved; and (v) counsellors and PCPs (if required) will attend weekly supervision and case review meetings with the mental health specialists (See Fig. 2).

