### Optimised usual care

Clinics assigned to the OUC will follow the usual care pathway with some adjustments. The existing SINA care pathway for mental health varies depending on availability of the lay counsellor. If a counsellor is present, PCPs refer patients with distress symptoms for further evaluation, using tools like PHQ-4, PHQ-9, GAD-7 [42], and suicide risk assessment. If depression or anxiety is detected, counselling therapy is provided. In clinics without a counsellor, there is no formal system for identification of mental illness. As part of the OUC, we will introduce following changes: (i) all physicians will administer the PHQ-2 screening for depression to all patients aged ≥ 18, and if the PHQ-2 score is ≥ 3, physicians will refer patients to the counsellor and provide a leaflet with information about depression symptoms, treatment options, and nearby free mental health services and (ii) counsellors will be hired for clinics where there is not one available currently, who will screen patients using PHQ-9 and provide the usual care counselling therapy for those scoring ≥ 10.

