#### Secondary outcomes—implementation

Secondary implementation outcomes include:The reach of screening as the percentage of people attending clinics who participated in screening for depression (PHQ-2 and PHQ-9) at least once.Adoption of the intervention will be determined at 3 and 6 months through referral rates (number of patients referred for treatment divided by number of eligible patients). We will consider referrals, including within primary care settings and to specialised facilities if required. We will track the number of healthcare staff invited to training, those who attend, and the average number of supervision or case review meetings attended by staff each month. These metrics will be assessed in the 3rd and 6th month follow-up after the start date.The implementation of the CC components will be assessed using treatment engagement and dropout rates. We will determine the enrollment, completion, and dropout rates for psychotherapy (BA therapy in intervention clinics and any psychotherapy delivered in control clinics). Individuals who attend ≥ 2 sessions will be categorised as ‘engaged with BA/any psychotherapy’, whereas those attending < 2 sessions will be considered dropouts. We will also evaluate the prescription and adherence rates of antidepressants using the total number of antidepressants prescribed and the participants who complete their prescribed course of antidepressant medication captured through patient self-reporting.Sustainability will be assessed by comparing reach, BA completion and dropout, antidepressant prescription, and compliance rate over time.Equity in the treatment is the just distribution of treatment services, ensuring the participation of all individuals regardless of their socioeconomic status (SES) and demographic backgrounds. To ascertain equity, we will compare implementation outcomes mentioned above by SES and demographics (age, sex, ethnicity, education level).

Unless otherwise stated above, all outcomes will be recorded and compared across allocation groups, where feasible at all time points (3, 6, and 12 months after the start date).

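### Reach of screening divides by everyone attending although only adults are screened, so it understates adult coverage wherever minors attend

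*Protocol article*

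**What the plan says.** In the protocol article, Table 1 (Study design), key secondary outcome 11, reach of screening is RS = sd/nc. Here sd is the number screened for depression and nc "denotes the total number of individuals attending the clinics". Under Secondary outcomes—implementation it is described as "The reach of screening as the percentage of people attending clinics who participated in screening for depression (PHQ-2 and PHQ-9) at least once". Neither place restricts the denominator by age.

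The screening itself is restricted. In the intervention clinics the Collaborative care model section provides "two-stepped systematic identification of depression for all people aged ≥ 18". In the control clinics the Optimised usual care section says that "all physicians will administer the PHQ-2 screening for depression to all patients aged ≥ 18".

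The Recruitment section is looser: "All patients attending the trial clinics will be screened by trained PCPs for depressive symptoms initially using the PHQ-2", with no age given. It adds that those positive on the PHQ-2 (score 3 or more) "will be referred to the counsellors for assessment using the PHQ-9", so the second instrument reaches only part of those screened.

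The neighbouring outcomes in Table 1 are built differently. Items 12 and 14 (reach of treatment, treatment enrolment) divide by people eligible for treatment, item 13 (adoption) by people eligible for referral, and items 15 and 16 (completion, dropout) by people enrolled.

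**The concern.** A person under 18 who attends a trial clinic counts in the denominator of RS and can never enter the numerator. The Study setting section describes clinics that offer a full range of primary care, and the age limit on screening would be needless if only adults came. Attendance by minors is therefore implied, though the article does not state it or give a number.

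If minors do attend, a clinic that screens every adult still scores below 100%, and two clinics with identical adult coverage can report different values. Age mix is not among the three minimisation factors (clinic size, electronic records, counsellors) and is not a named covariate in Statistical methods. Table 1 also carries reach into sustainability and equity (items 17 and 18). If that includes reach of screening, a change in child attendance over time, or a different child share between subgroups, could look like decay or inequity.

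**Working it through.** **Inputs from the article.** Definitions of sd and nc (Table 1); screening from age 18 (Collaborative care model, Optimised usual care); 24 clinics allocated 1:1, so 12 per arm (Abstract); a log-link binomial model for clinic-level outcomes, which compares arms as a ratio (Statistical methods).

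**Inputs assumed, because the article gives none.** The adult share of attenders, its variation between clinics, and adult coverage.

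**The plan's own figure.** There is none for this outcome. The nearest is the number to screen: 720/(0.10 × 0.60) = 12,000, which reproduces. It serves recruitment and does not bear on RS.

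**Step 1: what RS equals.** Let a be the share of attenders aged 18 or over and s the share of those adults who are screened. For N attenders, sd = N × a × s and nc = N, so RS = a × s. With s = 1 the highest possible value is a.

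**Step 2: effect on the level.**

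| Assumed adult share a | Ceiling of RS | RS when true adult coverage is 80% |
|---|---|---|
| 90% | 90% | 72% |
| 80% | 80% | 64% |
| 70% | 70% | 56% |
| 60% | 60% | 48% |
| 50% | 50% | 40% |

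**Step 3: effect on the comparison of arms.** The ratio of RS is (a1 × s1)/(a0 × s0).
- Equal adult shares: a cancels and the ratio is s1/s0, which is correct.
- Unequal shares with equal coverage: 0.65/0.55 = 1.18, or 0.60/0.55 = 1.09, where the truth is 1.00.

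**Step 4: how much imbalance chance could produce.** Take a mean adult share of 60%, equal true coverage, clinics weighted equally and simple randomisation. Then SE(log ratio) ≈ (SD/0.60) × √(2/12), and the 95% range is exp(±1.96 × SE).

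| Assumed between-clinic SD of a | SE(log ratio) | 95% range of the ratio when the truth is 1 |
|---|---|---|
| 5 points | 0.034 | 0.935 to 1.069 |
| 10 points | 0.068 | 0.875 to 1.143 |
| 15 points | 0.102 | 0.819 to 1.221 |

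A simulation of clinic adult shares under the same assumptions gave 0.94–1.07, 0.87–1.14 and 0.82–1.22. The ranges are centred on 1: this is extra variance, not a shift in one direction.

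**Step 5: after the change.** With attenders aged 18 or over in the denominator and a recorded PHQ-2 in the numerator, RS = s. The ceiling is 100% whatever the age mix, and Steps 2 to 4 no longer apply.

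**The case against.** The best defence is that the article is using shorthand. The Recruitment section also speaks of all attending patients without an age, although the arm descriptions make plain that adults are meant. An age filter on an aggregate count could sit in the full protocol or analysis plan, which are not shown. The clinic-level covariates are introduced as examples, so age mix could be added. Table 3 schedules screening at baseline too, and a stable age mix cancels from relative change within a clinic. The outcome is secondary.

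Part of this stands. The consequence is limited, and the intention may well be adults. But the denominator is not a detail left open: it is written out as a formula, while the neighbouring items use eligible or enrolled people. The loose sentence in Recruitment conflicts with the two arm descriptions, so it is one more place to align and does not rescue the formula.

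Three stronger readings are tempting, and the documents do not support them.
- *RS measures age mix rather than implementation.* It is the product of adult share and adult coverage, so at a given age mix it still rises and falls in proportion to coverage.
- *The comparison of arms is biased.* Clinics are randomised, so age mix has no average effect on the contrast, and equal adult shares cancel in the ratio. Only chance imbalance remains.
- *Both instruments are required, which would cap the rate at the PHQ-2-positive share.* The bracket naming the PHQ-2 and PHQ-9 most naturally lists the tools of the two-stage process. Counting people screened at least once fits that reading, and Table 1 asks only for the number screened. Requiring both would contradict the pathway, in which a PHQ-2-negative adult is fully screened. This is an ambiguity of wording, not an error.

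**Conclusion.** The mismatch between numerator and denominator stands in the text and is worth correcting. As written, and wherever minors attend, RS understates adult coverage, cannot reach 100%, and brings age-mix noise into a comparison of 12 against 12 clinics.

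Its size cannot be determined from the article. At an assumed adult share of 50% to 90%, coverage of 80% reads as 40% to 72%. Chance imbalance could move the ratio of arms by about 7% either way if the adult share varies between clinics with an SD of 5 points, and by about 20% at 15 points. These figures rest on assumed age mixes and on equal coverage in all clinics. If no minors attended, the problem would vanish.

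The primary reach outcome, whose denominator is people with a PHQ-9 score of 10 or more, is not affected, nor is the primary PHQ-9 outcome.

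**What to change.** - In Table 1 item 11 and in Secondary outcomes—implementation, define nc as distinct individuals aged 18 or over attending in the period, and sd as those among them with a recorded PHQ-2 at least once.
- Make the Recruitment section agree with the Collaborative care model and Optimised usual care sections on who is screened.
- As a clarification only, state that the bracket names the tools of the two stages and does not require both. Report PHQ-9 completion separately, as the number with a recorded PHQ-9 divided by the number with a PHQ-2 score of 3 or more.

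The cost is a short change of definition and an age filter on the attendance count. The real burden falls on clinics without electronic records, which need an adult tally from their attendance registers. Because recruitment is already under way (Trial status), it should be settled soon, as adult counts from paper registers may be hard to rebuild later.
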